# Internet delivered, non-inferiority, two-arm, assessor-blinded intervention comparing mindfulness-based stress reduction and cognitive-behavioral treatment for insomnia: a protocol study for a randomized controlled trial for nursing staff with insomnia

**DOI:** 10.1186/s13063-022-06986-3

**Published:** 2022-12-16

**Keywords:** Sleep disorders, Insomnia, CBT-I, MBSR, Internet, COVID-19, Treatment

## Abstract

**Background:**

Insomnia and poor sleep quality are highly prevalent conditions related to coronavirus disease 2019 (COVID-19) complications among clinical nurses. Although cognitive behavioral therapy for insomnia (CBT-I) is a first-line treatment, CBT-I suffers from several major drawbacks. This study investigates whether the application of the internet-delivered mindfulness-based stress reduction (iMBSR) intervention will produce effects that are non-inferior to the internet-delivered CBT-I (iCBT-I) intervention in reducing the severity of insomnia in clinical nurses with insomnia at the end of the study.

**Methods:**

This study protocol presents an internet-delivered, parallel-groups, assessor-blinded, two-arm, non-inferiority randomized controlled trial. The primary outcome is sleep quality, assessed by the Insomnia Severity Index. Secondary outcomes include depression, dysfunctional beliefs, five facets of mindfulness, and client satisfaction.

**Conclusion:**

It is expected that this study may address several gaps in the literature. The non-inferiority study design is a novel approach to evaluating whether a standardized, complementary treatment (i.e., MBSR) is as practical as a gold standard treatment rather than its potential benefits. This approach may lead to expanded evidence-based practice and improve patient access to effective treatments.

**Trial registration:**

Trial registration number: ISRCTN36198096. Registered on 24th May 2022.

**Supplementary Information:**

The online version contains supplementary material available at 10.1186/s13063-022-06986-3.

## Introduction

### Background and rationale {6a}

#### Background

The outbreak of coronavirus disease 2019 (COVID-19) is an emotionally challenging time for healthcare workers (HCWs), associated with a substantial increase in the prevalence of physical and mental health problems [1, 2]. For example, the nursing staff is more likely to report for a COVID-19 positive test [3, 4]. Following the COVID-19, the demand for medical personnel surged considerably. The lack of healthcare workers has led to a dramatic increase in work overload, as well as an elevated psychological distress among HCWs [5]. Additionally, numerous studies during the COVID-19 pandemic have suggested that clinical nurses are at high risk of developing depression, anxiety, and insomnia compared with general populations [6–9]. During the COVID-19 pandemic, research shows a high prevalence of pandemic-related sleep disturbance among clinical nurses [4, 10, 11].

Insomnia is a highly prevalent complaint in primary care settings and it is characterized by difficulties in sleep initiation or maintenance, which occur at least three times per week for less than 3 months [12]. The consequences of insomnia range from loss of productivity, absenteeism, and job accidents [13] to cognitive performance [14]. Also, insomnia has bidirectional causation and interactive relationships with anxiety [15], depression [16], and difficulties with emotion regulation [17]. For clinical nurses, insomnia impact of quality of life [18], job satisfaction and the care of patients [19], work performance [20], immune system [21], and the turnover intention [22]. Therefore, it is extremely important to reduce the severity of insomnia symptoms among nurses during the pandemic. However, there have been insufficient preventative interventions on clinical nurses’ present sleep disruption status. Despite the prevalence and clinical significance, insomnia is frequently underdiagnosed [23] and, consequently, undertreated. Untreated insomnia carries the burden of added lower job productivity and quality of life [5, 24] and physical health risks, such as cardiovascular disease [25], stroke [26], hypertension, and diabetes [27]. Insomnia is a highly prevalent problem related to COVID-19 complications for nurses [7]. During the current pandemic, nurses may be at a higher risk of mental health problems than doctors [28]. Being a frontline nurses is independently associated with higher levels of depression, anxiety, and insomnia [29]. In comparison to non-medical HCWs, HCWs in direct contact with COVID-19 patients had significantly higher levels of insomnia, anxiety, and depression [30]. Additionally, contact with COVID-19 patients is independently associated with elevated risk of sleep disturbance [31]. Although addressing the needs of nurses is a high priority, information to inform such contributions is limited.

The pharmacologic treatments for insomnia have side effects and increase dependency [32]. Therefore, psychological interventions must be immediately implemented to promote the mental health of nurses exposed to COVID-19. Among non-pharmacological treatments, CBT-I is a multi-component intervention for insomnia and is recommended as first-line therapy [33]. The CBT-I addresses a wide variety of psychological issues, from modifying cognitive beliefs [34] to reducing psychiatric symptoms [35, 36]. CBT-I effectiveness for the treatment of insomnia comorbid with other disorders has been also well-documented [37–40]. Although CBT-I is a low-risk, productive, and durable treatment, some drawbacks are related to effectiveness and accessibility.

Regarding effectiveness, a significant number (30 to 40%) of insomnia patients did not respond or remit, and over half (50–60%) experienced a varying degree of insomnia symptoms following a CBT-I intervention [41]. One potential explanation is poor adherence to treatment [42]. Several core components of CBT-I (e.g., sleep restriction and stimulus control) can be difficult to implement and often result in a short-term worsening of symptoms and patient discomfort [43]. While CBT-I is effective for the treatment of insomnia comorbid with depression, this intervention may not adequately address the numerous factors that contribute to the development and maintenance of insomnia [35]. Regarding accessibility, main causes of limited access to insomnia treatments are identified. First, despite significant attempts to expand the numbers of CBT-I qualified experts the accessibility of CBT-I is still mostly restricted to clinical settings or major cities [44]. Second, the CBT-I requires a highly qualified therapist who is not geographically available. In addition to the lack of CBT-I therapists, professionals are uninformed of available therapy options. Finally, insurance payment for CBT-I may be inadequate, especially if it is provided by mental health professionals who are not physicians (such as psychologists). These barriers highlight the need for approaches that could be implemented more easily in public. Clearly, there is a need to improve and expand the available insomnia treatment options. Mindfulness-based interventions (MBIs) are additional therapies that may solve this drawback of CBT-I. A complementary and supplementary treatment, which can address the CBT-I limitations, incorporates mindfulness.

Mindfulness is a mind’s awareness that emerges through deliberate concentration of the moment, in the present moment, and on non-judgmentally moment-by-moment experience with an attitude of curiosity, openness, and acceptance [45, 46]. MBIs are the type of non-pharmacological psychotherapy that has grown dramatically in recent years for several health-related disorders, including sleep problems and insomnia [47–50]. The MBIs effects are strong in studies primarily aimed at improving sleep [51]. Mindfulness techniques help individuals recognize earlier and more skillfully respond to the chronic or maladaptive patterns of mind. MBIs aim to directly reduce pre-sleep arousal and may avoid the short-term unpleasant consequences sometimes seen in CBT-I [52].

Clinical nurses also experience other symptoms comorbid with sleep disturbance, which CBT-I may not target, such as distress generated by stressful events [53] and difficulty with emotion regulation [54]. During the COVID-19, nursing staff experienced a great deal of physical and mental health issues, such as fatigue, sleep disorders, and burnout. Having to tell patients bad news is one of the difficult yet inevitable part of the medical profession. To maintain their own emotional equilibrium and mental wellbeing, they must be provided with the skills and training to be able to regulate such intense emotions. Mindfulness is related to positive emotion and life satisfaction [55], job productivity, and well-being [56]. Higher mindfulness levels are negatively associated with anxiety, psychological distress, and depression [57, 58]. For nurses, mindfulness is related to job performance, job satisfaction, and employee well-being [59]. Regarding coping with stressful events, the promotion of emotion regulation skills is suggested to underlie the benefit of mindfulness [60, 61]. One randomized controlled trial has compared an MBI to CBT-I [62]. The study revealed no significant differences in long-term efficacy for reducing insomnia severity. An online group mindfulness training program showed that mindfulness training via videoconferencing may be an effective intervention for stress reduction during the COVID-19 pandemic [63]. The “CoPE It” programs, E-mental health mindfulness-based and skills-based and consists of techniques of MBSR, help in reducing psychological distress in times of COVID-19 [64].

While individuals have the above-mentioned difficulties in accessing an appropriate insomnia intervention, at the same time, COVID-19 instructions and restricting policies (e.g., physical distancing) to minimize the risk of infection have made more difficult to seek and attend treatment. The Internet delivery of mental health services is a technological revolution that offers the possibility of expanding more accessible and cost-effective psychological interventions [65]. Meta-analytic findings have shown that Internet-based therapies are effective for insomnia [66, 67]. Recent research has demonstrated that Internet-based cognitive-behavioral therapies are an efficient and promising approach for various conditions, such as insomnia [68]. Compared with traditional face-to-face interventions, internet-delivered interventions provide widespread access and dissemination and increase cost-effectiveness [69, 70].

### Objectives {7}

The objective of this study is:To investigate whether the application of the internet-delivered MBSR intervention will produce effects that are not inferior to those of the internet-delivered CBT-I intervention in reducing the severity of insomnia in clinical nurses with insomnia at the post-intervention (8 weeks)To examine the effectiveness of an iCBT-I intervention to improve insomnia symptoms, dysfunctional beliefs and attitudes about sleep, depressive symptoms, mindfulness aspects, and quality of life in nursesInvestigate whether internet-delivered MBSR intervention could improve insomnia symptoms, dysfunctional beliefs and attitudes about sleep, depressive symptoms, mindfulness aspects, and quality of life in clinical nurses

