#### IMBSR group

The iMBSR intervention will be delivered in eight 2.5-h weekly sessions [74, 75], plus one 6-h weekend intensive silent retreat. The program is intended to facilitate increased awareness of one’s typical internal and external reactions to stress and introduce meditation techniques to promote healthy responses to stress. The core components of the IMBSR program comprise: (*a*) motivational interview; (*b*) physiological and psychological response to go; and (*c*) engage in a combination of the three major formal mindfulness practices (mindful hatha yoga sitting meditation and the body scan); (*d*) information on the effect of stress on health and options for mindful versus reactive responses to stress including non-judging, acceptance, patience, non-striving, and letting; and (*e*) course overview and relapse prevention. The program will be started with a module on motivation and readiness for change and treatment engagement and will be finished with a module for relapse prevention (for a more thorough explanation, see the supplemental data: appendix 2: part two).

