#### ICBT-I group

The CBT-I group format is typically delivered over six to eight sessions [76–78]. The CBT-I is a multi-component intervention that will be administered and structured based on eight 2-h weekly sessions. The core components of the ICBT-I program comprise the following: (*a*) motivational interview, (*b*) sleep hygiene education; (*c*) sleep restriction; (*d*) stimulus control, (e) cognitive therapy, and (*f*) course overview and relapse prevention (for a more thorough explanation, see the supplemental data: appendix 2: part one).

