### Data management {19}

The data will be collected via the Internet. The participants will complete the primary and secondary outcomes at three-time points: time 1: pretreatment to allocation, including baseline (week 1); time 2: immediately after the intervention, including post-treatment assessment (week 10), and time 3: 1-month follow-up (week 14). The data will be automatically coded and depersonalized and stored on a secure server. Before recruitment, the study protocol was designed with a concentrate on ensuring data quality through standardization of data collection processes. Data collection instruments were designed with validated items. Also, instrument guides were utilized as a reference for data collectors and supervisor, which included instructions for how to use instruments, definitions, and interpretation guidelines for each question. Also, all research team members received a comprehensive refresh course in the context of psychological assessments and ethics in clinical research. The supervisor ensure that each operation will be performed to a standard.

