## Statistical methods

### Statistical methods for primary and secondary outcomes {20a}

Main analyses will be conducted on the intent-to-treat (ITT) approach, including all randomly allocated participants, regardless of attendance. The last observation carried forward (LOCF) method is one way to handle missing data. In LOCF approach, the missing data are replaced by the last observed value of that variable. The time points for the observations of missed values will be reported. Descriptive statistics will be utilized to present the continuous variables as the means and SDs and categorical variables as the numbers and percentages.

To determine whether the IMBSR is inferior to ICBT-I, the confidence interval approach was used. Non-inferiority analysis will be assessed using an *F* test statistic generated from the linear mixed model and confidence intervals [86]. This tests whether the difference between the group means is statistically larger than the non-inferiority margin (clinically significant difference) and if the upper limit of the one-sided confidence interval of the difference between the group means is less than the pre-specified margin of non-inferiority. A non-inferiority margin of 4 points on ISI is chosen for the analysis. This means that the mean difference between the groups should not be more than 4 points in favor of ICBT-I, to establish noninferiority of IMBSR. Repeated-measures analyses of variance (ANOVAs) two (condition: iMBSR *vs*. iCBT-I) × three (time point: time1, time2, time3) will be designed to compare the main treatment effects of the conditions on secondary outcomes. The values of effect sizes are presented as partial eta squared and Cohen’s *d.*

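### The objective sets the non-inferiority question at post-intervention, the abstract sets it at the end of the study, and the decision rule names no visit

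*Protocol article*

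**What the plan says.** Objectives {7} poses the non-inferiority question "in reducing the severity of insomnia in clinical nurses with insomnia at the post-intervention (8 weeks". The Background paragraph of the abstract poses it "in reducing the severity of insomnia in clinical nurses with insomnia at the end of the study".

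Data management {19} schedules three assessments: "time 1: pretreatment to allocation, including baseline (week 1", then "time 2: immediately after the intervention, including post-treatment assessment (week 10), and time 3: 1-month follow-up (week 14". The treatments last eight weekly sessions: "eight 2-h weekly sessions" for iCBT-I and "eight 2.5-h weekly sessions" for iMBSR, the latter with an added retreat.

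The abstract's Methods paragraph names the endpoint without a time: "The primary outcome is sleep quality, assessed by the Insomnia Severity Index". The Primary outcome section and Sample size {14} also give no visit.

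Statistical methods {20a} takes the primary test from a linear mixed model and declares non-inferiority if "the upper limit of the one-sided confidence interval of the difference between the group means is less than the pre-specified margin", the margin being 4 ISI points. No visit or contrast is named. The layout of two conditions by three time points is attached to the secondary outcomes only.

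**The concern.** A non-inferiority verdict is one confidence limit set against one margin, so the visit at which the difference is taken is part of the hypothesis. Here the two statements of the primary aim point to different visits. The immediate effect of treatment and the effect a month after it ends are different questions, and the difference between arms need not be the same at both.

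This is more than detail left to a fuller document. The article states its aim twice, inconsistently, and states a decision rule that fits either version. With results from both visits in hand, a claim at whichever visit passes could be defended from the text.

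**Working it through.** **1. How many visits are really in play.**

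| Place | Label | Most natural visit |
|---|---|---|
| Objectives {7} | post-intervention, 8 weeks | time 2 |
| Abstract, Background | end of study | time 3 (week 14), the last assessment |
| Data management {19} | post-treatment, week 10 | time 2 |
| Statistical methods {20a} | none | undetermined |

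Baseline is in week 1. Eight weekly sessions in weeks 2 to 9 would place an assessment straight after treatment in week 10. So 8 weeks (treatment length) and week 10 (study week) can be the same visit; this is an inference from the schedule. Two candidates remain: week 10 and week 14.

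**2. The plan's own figure.** Sample size {14} gives 64 evaluable (32 per arm at 1:1), margin 4, one-sided 5% and 80% power. It gives no SD, so 64 cannot be reproduced from stated inputs. Solving backwards with a true difference of 0:

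SD = 4 / (1.645 + 0.842) × √(32/2) = 6.43

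SE = 6.43 × √(2/32) = 1.61

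This SD is implied by the sample size, not stated.

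**3. Success allowed at either visit.** Take a true deficit of 4 points at both week 10 and week 14. Each test alone passes with probability 0.05. For estimates with correlation ρ (assumed; bivariate normal):

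P(either) = 0.05 + 0.05 − P(both)

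| ρ | P(both) | P(either) |
|---|---|---|
| 0.3 | 0.007 | 0.093 |
| 0.5 | 0.012 | 0.088 |
| 0.7 | 0.020 | 0.080 |

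These rates do not depend on the SD.

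**4. The two visits can give different answers.** Suppose, for illustration, that the true deficit is 4 at week 10 and 2 at week 14. The chance of passing is Φ((4 − true difference)/SE − 1.645). At week 10 this is Φ(−1.645) = 5%. At week 14 it is Φ(2/1.61 − 1.645) = 34%. With an assumed SD of 5 (SE 1.25), the week 14 figure is 48%. Each is a proper test at its own visit, but the choice of visit changes the verdict.

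**5. Gain from baseline ISI as a covariate.** If baseline and week 10 ISI correlate at r (assumed), the variance of the difference is multiplied by 1 − r² and power is Φ(4/SE − 1.645), with 32 per arm and SD 6.43:

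| r | 1 − r² | SE | Power |
|---|---|---|---|
| 0 | 1.00 | 1.61 | 80% |
| 0.3 | 0.91 | 1.53 | 83% |
| 0.4 | 0.84 | 1.47 | 86% |
| 0.5 | 0.75 | 1.39 | 89% |

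The variance factor does not depend on the SD; the power column does.

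**The case against.** The formal objective does name a visit. It ties the non-inferiority question to post-intervention, and the schedule places the post-treatment assessment immediately after the intervention. Choosing the more favourable visit would mean departing from that objective, and the abstract's wording may simply be loose. This stands in part: the objective points to one visit, and it would be wrong to say that the document ties the question to none. It does not remove the conflict, because the abstract gives another time for the same question and the analysis section does not decide between them.

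A reader might infer a further conflict between 8 weeks and week 10. The documents do not support that, since the two labels fit one visit counted differently. A wording repair is enough.

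A reader might also infer that the primary test is the overall condition effect across all three visits, which averages in a baseline where randomised arms do not differ in expectation. A true 4-point deficit at both later visits would then appear as (0 + 4 + 4)/3 = 2.67, and false non-inferiority would be 24 to 31% (SD 6.43, correlation 0.7 to 0.3). The text does not exclude this reading, but it does not state it: the three-visit layout and its main effects are given for secondary outcomes only. These figures therefore do not describe the planned analysis.

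Finally, covariates are commonly left to an analysis plan. That is fair, and baseline adjustment is offered here as an efficiency gain, not as the correction of an error.

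**Conclusion.** The point holds as a contradiction over the primary visit: week 10 by the objective, most naturally week 14 by the abstract, with a decision rule that chooses neither. If either visit could count, the false non-inferiority rate would be about 8 to 9% instead of 5%, for assumed between-visit correlations of 0.3 to 0.7 and a true deficit exactly at the margin at both visits. This measures what the wording permits; nothing in the article says that the authors intend to choose. The reading of study end as week 14, and of 8 weeks as week 10, are inferences from the schedule. The repair should be made before results are seen, but it affects no sample size or data collection.

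**What to change.** Use one sentence, in the same words, in the abstract, Objectives {7} and Statistical methods {20a}: the primary estimate is the iMBSR minus iCBT-I difference in mean ISI at the post-treatment assessment (week 10), and non-inferiority is concluded if the upper one-sided 95% limit for that difference is below 4 points. Replace the 8-week label with the scheduled week, drop the reference to study end in the abstract's aim, and state that week 14 is secondary. Week 10 is proposed because it fits the objective as written.

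In {20a}, name the estimate as the week 10 contrast from the mixed model with baseline ISI as a covariate.

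The cost is wording in three places and one covariate that is already collected from every participant. No new data, visits or participants are needed.

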### Trial design {8}

This study is designed as a non-inferiority randomized controlled, Internet-delivered, parallel-group, assessor-blinded, two-arm trial comparing iCBT-I with an iMBSR. The study flowchart is displayed in Fig. 1. The SPIRIT (Standard Protocol Items: Recommendations for Intervention Trials) checklist of information was used to report a randomized trial [71] (see supplemental data: appendix 1).

